#### 2.7.2 Data collection.

Researchers are required to fill in the collected data on paper case report forms according to the research protocol requirements, and trained personnel will input them into the specially established electronic data capture (EDC) system. At the end of the study, researchers will submit case report forms for all selected patients to the data management center, which should include complete and signed content. Personally identifiable participant information, such as name and gender, will be replaced by codes throughout the study and will remain confidential, with only the project manager or relevant doctors aware of the patient’s personal information. Any reports on the results of this study will not reveal any identifiable information about the patients.

#### 2.7.3 Statistical methods.

Local recurrence is defined as tumor recurrence in the lumen or in the mesorectum and must be confirmed by a pathological biopsy. A distant metastasis is defined as a metastasis that is discovered in the liver, lung, bone, or other sites by CT, MRI, or radionuclide scanning, with or without pathological examination. Disease-free survival (DFS) is defined as the absence of local recurrence, distant metastasis, and death from any cause. Overall survival (OS) is defined as the absence of death from any cause. The duration of follow-up will be calculated from the date of surgery to the event of interest or the last follow-up date.

To determine the consistency between the PTC drug sensitivity results and clinical outcomes, the following methods will be employed (Table 2): positive consistency rate = a/(a + c) × 100%; negative consistency rate = d/(b + d) × 100%; overall consistency rate = (a + d)/(T1) × 100%; sensitivity = a/(a + b) × 100%; and specificity = d/(b + d) × 100%.

**Table 2 pone.0326760.t002:** Consistency test of recurrence and metastasis cases.

Drug sensitivity test	Clinical efficacy		Sum
	CR + PR	SD + PD	
**Effective**	a	B	a + b
**Invalid**	c	D	c + d
**Sum**	a + c	b + d	T1

The results will be presented as median values or means ± standard deviations for continuous variables and as numbers (percentages) for categorical variables. The t test and Wilcoxon rank sum test will be used to compare continuous variables, and chi-square analysis/Fisher’s exact test will be used to compare categorical variables. Survival analysis will be conducted using the Kaplan-Meier curves. Log-rank test to compare the primary endpoint between different arms in the presence of censoring. A P value of 0.05 or less is considered statistically significant. All the statistical tests will be two-sided. All analyses will be performed using SPSS Version 26.0 (SPSS Inc., Chicago, IL).

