In 2020, [name] team developed a novel in vitro model called patient-derived tumor-like cell clusters (PTCs) [14]. Three-dimensional microspheres are formed by the self-assembly of tumor cells and tumor stromal cells from patient samples after cutting, digestion, and proliferation. The resulting PTCs include various cells derived from tumor tissue, such as tumor epithelial cells, tumor stem cells, fibroblasts, and immune cells, which can simulate the tumor microenvironment to a certain extent. The PTC model is highly similar to the original tumor tissue in terms of morphology, pathological characteristics, genetic background, and other dimensions [15]. For gastrointestinal tumors, the consistency between PTC drug sensitivity test results and clinical efficacy reached 96.6% [14]. Therefore, the high accuracy of PTC drug sensitivity testing technology has been preliminarily confirmed.

On the basis of the above background, this study aims to conduct a multicenter randomized controlled trial to compare the consistency between the in vitro PTC drug sensitivity test results and the clinical prognosis of CRC patients. The goal is to explore the decision-making value and guiding significance of this technology for assisting in precision treatment of CRC. This study will provide a valuable reference for achieving individualized and precise treatment of CRC patients and offer real-world data support for the clinical application of PTC drug sensitivity testing technology.

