### 2.7 Statistical analysis

#### 2.7.1 Sample size.

Our study is a noninferiority study. With a bilateral α = 0.05, a test efficacy of 1-β = 80%, a 3-year disease-free survival rate of 75%, and a noninferiority threshold of 20%, the estimated minimum sample size for each group is 74. Considering a dropout rate of 20% (according to EMEA [26], ICH [27], and FDA [28] guidelines and previous studies [29]), we ultimately decided to include 100 patients in each group, totaling 200 patients across both groups.

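### The overall consistency rate for PTC result against outcome depends on the margins and can be high for an uninformative test, so it should not be read alone or serve as the main measure

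*Protocol article*

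**What the plan says.** Section 1 of the protocol article gives the aim of the trial as to "compare the consistency between the in vitro PTC drug sensitivity test results and the clinical prognosis of CRC patients". The abstract and section 2.1 describe the aim in similar terms. Section 2.6 places consistency among the secondary endpoints; the primary endpoint is the 3-year DFS rate.

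Section 2.7.3 fixes how consistency is measured. Table 2 crosses the test result (Effective or Invalid) with clinical efficacy (CR + PR or SD + PD), and its title is "Consistency test of recurrence and metastasis cases". Five proportions are listed:

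- the two class-specific rates, "positive consistency rate = a/(a + c) × 100%; negative consistency rate = d/(b + d) × 100";
- the overall rate, "overall consistency rate = (a + d)/(T1) × 100";
- two further measures, "sensitivity = a/(a + b) × 100%; and specificity = d/(b + d) × 100".

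None of the five carries a chance value or a null. The log-rank test in the same section compares treatment arms. Chi-square or Fisher's exact test is named for categorical variables in general and is not tied to Table 2.

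**The concern.** The overall rate mixes two things: whether the test carries information, and how common Effective labels and good outcomes are. When both are common, agreement is high by coincidence. The positive rate a/(a+c) has the same weakness, because for an uninformative test it simply equals the share labelled Effective.

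A high share is plausible in the experimental arm, where section 2.4 has doctors choose the regimen from the PTC result. The article gives no figure for it.

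At stake is the reading of a stated aim of the trial. A rate of 65% or 70% could be reported as good agreement when the test says nothing about who relapses. Section 1 shows how such a figure can be read: after citing a raw consistency of 96.6% from a previous study, it concludes "Therefore, the high accuracy of PTC drug sensitivity testing technology has been preliminarily confirmed".

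**Working it through.** **The plan's own figure.** No target is stated for consistency. The only design figure that can be reproduced is the primary sample size in section 2.7.1, which uses "With a bilateral α = 0.05", 80% power, "a 3-year disease-free survival rate of 75" per cent and a margin of 20 points:

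n = 2 × 0.75 × 0.25 × (1.960 + 0.842)² / 0.20² = 73.6, so 74 per group.

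This agrees with the article, so 75% is the plan's working value for 3-year DFS.

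**Inputs for the check.**

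- s, the share with a good outcome: 0.75, from section 2.7.1. Using 3-year DFS in place of CR + PR is an assumption.
- q, the share labelled Effective: not stated, so a range is shown.

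**Uninformative test.** Under independence, a = qs, b = q(1−s), c = (1−q)s and d = (1−q)(1−s). The overall rate is then

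a + d = qs + (1−q)(1−s) = 0.25 + 0.5q at s = 0.75.

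| q | 0.50 | 0.60 | 0.75 | 0.80 | 0.90 | 0.95 | 1.00 |
|---|---|---|---|---|---|---|---|
| Overall rate by chance | 50% | 55% | 62.5% | 65% | 70% | 72.5% | 75% |

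**Informative test (illustrative).** Take q = 0.50, with 3-year DFS of 90% if Effective and 60% if Invalid, so that s = 0.75 again. The cells are a = 0.45, b = 0.05, c = 0.30 and d = 0.20.

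- Overall rate = 0.45 + 0.20 = 65%.
- Chance value = 0.5 × 0.75 + 0.5 × 0.25 = 50%.
- Kappa = (0.65 − 0.50)/(1 − 0.50) = 0.30.

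The useless test has the higher expected overall rate when 0.25 + 0.5q > 0.65, that is, when q > 0.80.

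**All listed measures side by side, useless test at q = 0.90.**

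| Measure | Useless | Informative |
|---|---|---|
| Overall (a+d)/T1 | 70% | 65% |
| Positive rate a/(a+c) | 90% | 60% |
| Negative rate and specificity d/(b+d) | 10% | 80% |
| Printed sensitivity a/(a+b) | 75% | 90% |
| Positive + negative − 100% | 0 | 40 points |
| Kappa | 0 | 0.30 |

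The overall and positive rates put the two tests in the wrong order. The other rows put them in the right order.

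**Sampling variation at n = 100.** In simulated pairs, the useless test shows the strictly higher overall rate in about 6% at q = 0.60, 33% at q = 0.75, 47% at q = 0.80 and 75% at q = 0.90.

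**Direct comparison of 3-year DFS by test result** (two-proportion z test, n = 100, all patients observed). It rejects in about 95% of trials for the informative test with an even split, and in about 4% for the useless test at q = 0.90. For a 30-point difference at q = 0.90 (78% versus 48%; 0.9 × 0.78 + 0.1 × 0.48 = 0.75), power falls to about 54%.

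**If Table 2 covers only relapsed patients.** Then 75% does not apply. With an assumed CR + PR share of 10% to 50%, and q from 0.1 to 0.9, the chance value lies anywhere from 18% to 82%.

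**The case against.** The strongest reply is that the overall rate is one of five listed measures. A reader might infer that the whole set cannot tell a working test from a useless one. The article does not support that: at q = 0.90 a specificity of 10% against 80%, and a/(a+b) of 75% (exactly the base rate) against 90%, separate the two plainly. That stands and limits the point to the overall and positive rates.

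Second, a reader might take about 70% as the plan's chance value. It is not. It needs q near 0.90, which is stated nowhere, and DFS used in place of Table 2's response columns. The reversal also depends on the comparator: a test with positive and negative rates of 80% each scores 80% overall, above the 75% maximum chance value in the table. This stands as well.

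Third, kappa, intervals and benchmarks are details that a condensed article may leave to a fuller document, and nothing prevents chi-square from being applied to Table 2. So the absence of kappa or a CI is not the finding. What remains is that section 2.7.3 does more than stay silent: it names the measures to be used, and one of them has no interpretable null.

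Fourth, no success threshold is attached to the rate, and section 1 calls the accuracy only preliminarily confirmed. That a high rate will be misread is a risk, not something the plan commits to.

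**Conclusion.** The point holds in a limited form. Of the measures fixed in section 2.7.3, the overall rate, and with it the positive rate, depends on the margins and can be high for a test that carries no information. With 75% 3-year DFS assumed as the good outcome, the chance value of the overall rate is 50% to 75% for q from 0.5 to 1. It exceeds the 65% of the illustrative informative test only when q is above 0.80. The listed negative rate, specificity and a/(a+b) do expose such a test, but the section neither combines them nor ties a test to Table 2.

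The matter deserves correction because consistency is presented as an aim of the trial. It is formally a secondary endpoint, and the primary endpoint and its 74 per group are untouched.

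**What to change.** In section 2.7.3:

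1. State that the overall rate will not be interpreted alone. Report it beside its chance value from the observed margins, qs + (1−q)(1−s), together with the positive rate + negative rate − 100% (or kappa) and a 95% CI.
2. Make the main measure of consistency a contrast that is null for an uninformative test. In the control arm, compare DFS between patients whose received regimen tested Effective and those whose regimen tested Invalid, giving the Kaplan-Meier difference at 3 years and the hazard ratio, each with a 95% CI.
3. Describe that contrast as an association. Control-arm regimens are chosen on clinical experience (section 2.4), so the two groups may differ in prognosis.

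The change is wording only. Both arms are tested and followed for DFS already, so it needs no new data, patients or procedures. The price is a figure that may look less favourable than a raw percentage, and a wide interval if few control patients received a regimen that tested Invalid. At q = 0.90, power for a 30-point difference is about 54% with 100 patients, and about 47% with the 80 left after the plan's 20% dropout.

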## 1 Background

Colorectal cancer (CRC) is a common gastrointestinal malignancy that seriously endangers human health. According to cancer statistics 2023 [1], CRC has become the third most common cancer in terms of both incidence and mortality rates. Approximately 25–30% of stage II CRC patients experience recurrence and metastasis within 5 years after surgery, whereas approximately 50–60% of stage III CRC patients experience recurrence and metastasis within 5 years after surgery [2,3]. In addition, 45–50% of patients with stage II-III disease develop liver metastases within two years after primary resection [4,5]. As the main adjuvant treatment for CRC surgery, multiple international clinical studies have shown that surgery combined with adjuvant chemotherapy can achieve a total 5-year survival rate of 60–70% and a total 5-year disease-free survival rate of 55–65% for high-risk stage II and stage III patients [6,7].

However, CRC is a malignant tumor with significant heterogeneity [8,9], and there are significant individual differences in drug sensitivity among patients. Even patients with the same pathological type and clinical stage who receive the same treatment plan have different prognoses and outcomes [10]. The selection of adjuvant chemotherapy regimens for different subgroups of patients remains controversial. Therefore, constructing a model that can accurately predict drug efficacy and guide personalized treatment for patients is one of the strategies for achieving precision treatment of CRC. Scientists have been dedicated to developing in vitro models for drug sensitivity testing over the past century, including cell lines, primary tumor cells [11], patient-derived organoids (PDOs) [12], and patient-derived tumor xenograft (PDX) mice [13]. However, owing to issues such as standardization, accuracy, and cycle, these methods have certain limitations in clinical application and struggle to achieve true clinical translation.

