### 2.4 Intervention

We plan to include 200 patients for analysis, with 100 in the experimental group and 100 in the control group. Both groups will undergo PTC drug sensitivity testing and whole exome sequencing (WES). For the experimental group, doctors will select adjuvant chemotherapy regimens on the basis of the PTC drug sensitivity test results. For the control group, doctors will determine adjuvant chemotherapy strategies on the basis of their clinical experience. The PTC drug sensitivity and WES results will be documented for humanitarian treatment reference after the study concludes or if patients withdraw from the study.

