### 2.5 Therapeutic schemes

#### 2.5.1 PTC drug sensitivity test.

Upon receiving the tumor tissue, the laboratory will verify the sample number and establish a sample file via the laboratory management system for data file management. After laboratory tests are conducted on the sample status (including temperature, time in vitro, and presence of leakage), sample processing and cultivation will be performed. After 2–7 days of cultivation, the formation of PTC clones will be observed via bright field microscopy. If PTC clones fail to form within 7 days, cultivation will be declared unsuccessful, and the patient will be withdrawn. If PTC clones are formed, open field photos will be retained to check for bacterial, fungal, and mycoplasma infections in the culture. Samples identified as negative will be subjected to drug sensitivity experiments [14].

We will test four commonly used adjuvant chemotherapy regimens in clinical practice [19]: fluorouracil+formyltetrahydrofolate (5-RU) [7], oxaliplatin+5-fluorouracil+formyltetrahydrofolate (FOLFOX) [20], irinotecan+5-fluorouracil+formyltetrahydrofolate (FOLFORI) [21,22], and cetuximab+5-fluorouracil+formyltetrahydrofolate [23,24]. For the screening experiment, a 96-well plate will be used, and each experimental group will be equipped with three parallel wells to ensure the reliability of the experimental data. Each sample will be collected twice, once after 0 days of dosing and once after 7 days of dosing. The automatic scanning system will be used to identify the number and area of all PTC clones in the hole. The area ratio of PTC clones (i.e., residual cell viability) after and before dosing will be calculated via the $p_{Ai}=\frac{S_{Ai,t}}{S_{Ai,t0}}$, $p_{A}=\frac{1}{n}\sum_{i=1}^{n}p_{Ai}$ formula [25], and the interpretation criteria are shown in Table 1. The higher the score is, the better the drug’s efficacy in killing tumors, and higher-scoring regimens are more recommended.

**Table 1 pone.0326760.t001:** Criteria for Judging the Drug Sensitivity of PTCs.

Lethality level	Lethality cell percent (%)	Remaining cell percent (%)
**Strong killing effect**	>0.7	0-0.3
**Effective killing effect**	0.3-0.7	0.3-0.7
**Stable**	0.1-0.3	0.7-0.9
**Drug resistant**	0-0.1	0.9-1
**Strongly drug resistant**	0	1

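### The consistency rates come from one crude table over arms, regimens and stages, so they can reflect how the regimen was chosen and the stage mix as well as PTC accuracy

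*Protocol article*

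**What the plan says.** Section 2.7.3 (Table 2) crosses the drug sensitivity result (Effective or Invalid) with clinical efficacy (CR+PR or SD+PD). It forms all rates from those four cells, including "overall consistency rate = (a + d)/(T1) × 100". No cell or rate carries an index for arm, regimen or stage. The caption reads "Consistency test of recurrence and metastasis cases".

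The other parts that bear on this are:

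- **Regimens (section 2.5.1).** "We will test four commonly used adjuvant chemotherapy regimens in clinical practice". All four contain fluorouracil with folinate, and three add one further agent. Table 1 ("Criteria for Judging the Drug Sensitivity of PTCs") gives one set of cut-offs for all of them. Regimens with higher scores are preferred.
- **Choice of regimen (section 2.4).** Both groups are tested. In the experimental arm, "doctors will select adjuvant chemotherapy regimens on the basis of the PTC drug sensitivity test results". In the control arm, "doctors will determine adjuvant chemotherapy strategies on the basis of their clinical experience".
- **Stage (sections 1 and 2.2.1).** Node-negative T3-4 and node-positive patients are enrolled together. The Background puts 5-year recurrence in stage II at 25–30% and says that "approximately 50–60% of stage III CRC patients experience recurrence and metastasis within 5 years after surgery".
- **Randomization (section 2.3).** Stratified by surgical center only.

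**The concern.** Randomization protects the comparison between arms. It does not protect the comparison of Effective with Invalid patients, which is observational. Two routes can make that comparison depend on something other than the assay.

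1. In the experimental arm the test selects the treatment. If the best-scoring regimen is given, few patients can be Invalid for what they received. Overall agreement then moves toward the proportion with a good outcome, whether or not the assay predicts anything.
2. In the control arm, suppose clinical experience leads to combinations more often in higher-stage patients, and suppose combinations reach the Effective threshold more often than the backbone alone. Effective then becomes partly a marker of higher stage and so of worse prognosis.

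Agreement between the test and clinical outcome is the first secondary endpoint and part of the study's stated aim. A rate that shifts with prescribing habits could make a useless assay look accurate or an informative one look weak.

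**Working it through.** **The plan's own figure.** The article gives no target or precision for the consistency rates. Its only sample size is for the primary endpoint: 2 × 0.75 × 0.25 × (1.960 + 0.842)² / 0.20² = 73.6, so 74 per group, as stated. Dividing by 0.8 gives 92.5, so 93, which the planned 100 covers. The sample size is not at issue.

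**Inputs for the illustration**

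- From the article: 1:1 allocation, 200 patients, mean 3-year DFS 75%.
- Assumed, not in the article: half the patients stage III; 3-year DFS 85% in stage II and 65% in stage III (mean 75%); DFS as the outcome in everyone; control-arm combinations in 30% of stage II and 80% of stage III; mean kill 0.25 for the backbone and 0.45 for combinations, SD 0.15; Effective means kill above 0.3; no information in the assay within stage and regimen.

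**Control arm**

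- P(Effective) = 1 − Φ((0.3 − mean)/0.15): 0.369 for the backbone, 0.841 for combinations.
- Stage II: 0.3 × 0.841 + 0.7 × 0.369 = 0.511. Stage III: 0.8 × 0.841 + 0.2 × 0.369 = 0.747. Average 0.629.
- a = 0.5 × (0.511 × 0.85 + 0.747 × 0.65) = 0.460; b = 0.629 − 0.460 = 0.169; c = 0.75 − 0.460 = 0.290; d = 0.25 − 0.169 = 0.081.
- DFS is 73.1% in Effective and 78.2% in Invalid patients. Odds ratio 0.76. Youden index 0.613 + 0.324 − 1 = −0.063. Overall consistency 0.460 + 0.081 = 54.1%.

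**Experimental arm.** With an uninformative assay, choice by score is unrelated to stage. If a share p is Effective, overall consistency is 0.75p + 0.25(1 − p) = 0.25 + 0.5p, with odds ratio 1. The share p is itself assumed:

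- p = 0.63, the same as in the control arm: 56.5%.
- p = 0.97, best-scoring regimen given and scores correlated at 0.5: 73.5%.
- p = 0.997, best-scoring regimen given and scores independent (1 − 0.159³ × 0.631): 74.9%.

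**Both arms pooled 1:1**

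| Experimental-arm Effective share | DFS gap (points) | Odds ratio | Youden | Overall consistency |
|---|---|---|---|---|
| 63% | −2.5 | 0.87 | −0.031 | 55.3% |
| 97% | −3.7 | 0.82 | −0.031 | 63.8% |
| 99.7% | −3.9 | 0.81 | −0.031 | 64.5% |

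**Which route matters more.** At p = 0.97 the arms differ by 73.5 − 54.1 = 19.4 points. With no link to stage, the control arm would show 0.25 + 0.5 × 0.629 = 56.4%. About 17 of the 19 points therefore come from the larger Effective share, and about 2 from stage-related choice.

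**When the association bias vanishes.** If control-arm choice is unrelated to stage, or Effective rates are equal across regimens, the control-arm odds ratio for an uninformative assay is 1. The dependence of overall consistency on the Effective share remains.

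**The case against.** The case on the other side has five parts.

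- **The links are inferred.** A reader might take it that doctors choose by patient risk throughout and that regimens kill differently in vitro. The article says neither. Risk-based choice can be supposed only for the control arm, and no killing data by regimen are given. This stands, and it is why the point is a risk and not a demonstrated bias.
- **Applying risk-based choice to all 200 patients overstates it.** That would give a Youden index of −0.063 and an odds ratio of 0.76. Half the patients follow the PTC result, which halves the Youden bias to −0.031. With 150 good and 50 poor outcomes, the standard error of the pooled Youden index at p = 0.97 is about 0.06, so the bias is about half a standard error. This stands.
- **The table may be a different one.** Its caption names recurrence and metastasis cases and its columns are response categories, whereas the illustration uses DFS in everyone. The article also does not map the five levels of Table 1 to Effective and Invalid. This stands as a limit on the numbers. It does not remove the lack of any split by arm or regimen.
- **Adjustment may be left to the SAP.** Fair for an omission. Here, however, the article states the formulas that will be used, and they are crude. Further analyses are not ruled out, so what needs settling is which result is the main one.
- **Stratified models answer another question.** Mantel-Haenszel and Cox estimates are associations, not consistency rates. This is right, so they should accompany the rates and not replace them.

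**Conclusion.** The point holds as a risk in the stated method for a secondary endpoint. One crude table, with regimen not randomized and stages of roughly two-fold different recurrence combined, can produce rates that reflect regimen choice and stage mix as well as PTC accuracy. The article does not show that this will happen, how large it would be, or in which direction.

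Under the assumptions above, the distortion of the association is modest: pooled odds ratio 0.81 to 0.87 and Youden about −0.03, where the true values are 1 and 0. The larger effect is on overall consistency, about 54% against 73.5% between arms for an assay that predicts nothing. That effect rests mainly on the assumed 97% Effective share in the experimental arm. It does not support the stronger inference that the pooled table measures confounding instead of accuracy.

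**What to change.** In section 2.7.3 and the SAP:

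1. Report the consistency rates separately by arm and by regimen received, with confidence intervals.
2. Add an estimate of the association between PTC result and outcome, stratified by arm, regimen and pathological stage (Mantel-Haenszel for the table, stratified Cox for time to event). State in advance how rarely used regimens will be merged.
3. Keep the pooled table as description only.
4. State which patients and which outcome Table 2 covers, since the strata depend on it.

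Scores should stay on their own scale. Rescaling them within regimen would change the question, because the test is used to rank regimens on the score itself.

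PTC results, treatment and staging are already recorded, so no new data, extra patients or clinical change are needed. The cost is precision. With about 200 × 0.25 = 50 events, four regimens by two stages leave about six events per stratum, and splitting also by arm about three. If 97% of the experimental arm is Effective, only about 3 of 100 patients there are Invalid, so the stratified estimate would rest largely on the control arm. The report should say so.

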In 1988, Sevin et al. pioneered the application of adenosine triphosphate biofluorescence tumor drug sensitivity detection technology (ATP-TCA) in 2D cultured ovarian cancer [11], but 2D models are incapable of replicating the spatial structure and heterogeneity of tumors within the body, nor can they capture the interactions between tumor cells and the tumor microenvironment (TME). Subsequent research focused on optimizing cultivation methods for 3D models, which better mimic in vivo conditions. For example, tumor spheroids, which better retain the morphological, physicochemical, and genetic characteristics of solid tumor cells, play crucial roles in the study of CRC invasion, metastasis, drug resistance mechanisms, and the development of targeted therapies and novel immunotherapies [38,39]. However, this technique faces challenges such as complex culture methods, a lack of vascular systems, disparities from real conditions, and difficulty in long-term stable cultivation.

PDOs are the result of a 3D cultivation technique that has gained attention in recent years. In 2015, M. van de Wetering et al. first reported the successful use of PDOs for high-throughput drug screening in CRC [40]. In 2018, G. Vlachogiannis et al. confirmed that PDOs cultured with tumor stem cells accurately predict the efficacy of anticancer drugs [12]. PDOs demonstrated 100% sensitivity and 93% specificity, with an 88% positive predictive value and 100% negative predictive value. Compared with spheroids, tumor organoids are highly complex and closely resemble the cellular composition, morphological structure, and physicochemical and genetic characteristics of tumors in vivo; they are also more suitable for biological transfection and can be cultured stably for longer periods in vitro. This makes organoids useful for high-throughput drug sensitivity studies, personalized precision therapy, and the establishment of biobanks. However, there are limitations. The success rate of cultivating CRC organoids is not yet satisfactory, particularly for metastatic CRC cases where cancer tissue can be obtained only through biopsy, with a modeling success rate of only approximately 70% [40,41].

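### The formula labelled sensitivity, a/(a+b), is the positive predictive value under the layout of Table 2, so that one index is mislabelled

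*Protocol article*

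**What the plan says.** Section 2.7.3 sets out how agreement between the PTC test and clinical outcome will be summarised. Agreement of this kind is the first secondary endpoint listed in section 2.6.

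Table 2 is a two-by-two table:
- **Rows, PTC test:** Effective holds a and b (row total a+b). Invalid holds c and d (row total c+d).
- **Columns, clinical efficacy:** CR+PR holds a and c (column total a+c). SD+PD holds b and d (column total b+d).

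Two cells are printed in upper case, B and D. The printed totals show that they are the same cells as b and d in the formulas.

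The text defines five indices on this table. Two are consistency rates: "positive consistency rate = a/(a + c) × 100%; negative consistency rate = d/(b + d) × 100". The third is "overall consistency rate = (a + d)/(T1) × 100". The last two are "sensitivity = a/(a + b) × 100%; and specificity = d/(b + d) × 100".

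**The concern.** Sensitivity and specificity both condition on the clinical reference: the first is the share of clinical responders whom the test called effective, the second the share of non-responders whom it called invalid. On Table 2 both should have a column total as denominator. Specificity does. Sensitivity as stated has a row total, so the two halves of the pair use different margins.

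A predictive value answers a different question (given an effective test result, how often is there a response?), and it moves with the response rate even when the test itself is unchanged. A reader who looks up sensitivity in the trial report would take the wrong number, for an analysis that serves the first-listed secondary endpoint and a stated aim of the study. The article itself treats the two measures as distinct when it reports organoid results: "PDOs demonstrated 100% sensitivity and 93% specificity, with an 88% positive predictive value and 100% negative predictive value".

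**Working it through.** **Figure to reproduce.** The article states no numerical sensitivity, so there is none to reproduce. The only design figure, 74 per group in section 2.7.1, follows from its own inputs and uses nothing from Table 2: 2 × 0.75 × 0.25 × (1.960 + 0.842)² / 0.20² = 73.6, rounded up to 74.

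**Step 1. Each formula against the layout of Table 2.**

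| Label in section 2.7.3 | Formula | Denominator | What it is |
|---|---|---|---|
| Positive consistency rate | a/(a+c) | clinical responders | sensitivity |
| Negative consistency rate | d/(b+d) | clinical non-responders | specificity |
| Overall consistency rate | (a+d)/T1 | all cases | overall agreement |
| Sensitivity | a/(a+b) | test-effective cases | positive predictive value |
| Specificity | d/(b+d) | clinical non-responders | specificity |

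Four of the five are valid for what they are called. One is not.

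**Step 2. Could the table simply be transposed?** If the rows were the clinical reference, a/(a+b) would be sensitivity, but specificity would then be d/(c+d). The article gives "specificity = d/(b + d) × 100". Neither orientation makes both formulas right.

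**Step 3. When do the two formulas differ?** For a > 0, a/(a+b) = a/(a+c) only if b = c. If b < c the stated formula is too high. If b > c it is too low.

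**Step 4. Size, on assumed cells.** The article gives no cell counts, so these only illustrate the algebra.

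| a, b, c, d (assumed) | Stated formula a/(a+b) | True sensitivity a/(a+c) | Difference |
|---|---|---|---|
| 90, 10, 30, 30 | 90/100 = 90.0% | 90/120 = 75.0% | +15.0 points |
| 20, 20, 5, 55 | 20/40 = 50.0% | 20/25 = 80.0% | −30.0 points |
| 30, 10, 10, 50 | 30/40 = 75.0% | 30/40 = 75.0% | 0 (b = c) |

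**Step 5. Dependence on the response rate.** Assume a true sensitivity of 90% and a specificity of 80%, and let p be the share of cases with CR or PR. The stated formula then returns 0.9p / (0.9p + 0.2(1 − p)).

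| p (assumed) | 10% | 25% | 50% | 75% | 90% |
|---|---|---|---|---|---|
| Stated formula | 33.3% | 60.0% | 81.8% | 93.1% | 97.6% |
| True sensitivity | 90% | 90% | 90% | 90% | 90% |

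For example, at p = 25%: 0.225 / (0.225 + 0.150) = 60.0%. The same test would be reported with a sensitivity anywhere from 33.3% to 97.6%, depending only on the case mix.

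**The case against.** The strongest reply is that little is lost. The endpoint in section 2.6 is named consistency, and all three consistency rates are valid. True sensitivity is already prespecified, as "positive consistency rate = a/(a + c) × 100", and anyone with the two-by-two table can recover every index. All of that stands and limits the consequence. It does not make the label right: "sensitivity = a/(a + b) × 100" is stated outright, and nothing else in the article corrects it. Because the rule is given and is wrong, it is not a detail left to an unseen analysis plan.

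A reader might infer more than the article supports, in four ways:

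- **That the test's diagnostic accuracy as a whole will be misreported.** Only one index of five is affected.
- **That the differences in the illustrations forecast the error.** They do not. Table 2 is titled as covering recurrence and metastasis cases and sorts them by CR+PR against SD+PD. The article gives neither the number of such cases nor their response rate. The 160 cases in the first illustration, 120 of them responders, are not a population taken from Table 2.
- **That the trial's result will be wrongly compared with the organoid figures.** The Discussion cites those as background, and no such comparison is planned. The passage shows only that the article distinguishes the two measures.
- **That the lack of a negative predictive value, confidence intervals or kappa is part of the error.** The article does not promise a negative predictive value, and intervals and kappa can properly be left to the analysis plan.

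**Conclusion.** The point holds in a narrow form. Under Table 2 as printed, the formula labelled sensitivity is the positive predictive value, and it is paired with a specificity that conditions on the other margin. The reported sensitivity will be wrong whenever b ≠ c and a > 0. The direction and size cannot be determined from the article, because they depend on a clinical response rate it does not give. The conclusion itself rests only on the table layout and the stated formulas. The illustrative differences rest on assumed counts, and the range over response rates on an assumed sensitivity of 90% and specificity of 80%.

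This is an error of definition in a secondary analysis. It does not touch the 3-year DFS comparison, the sample size, or the consistency rates themselves. It should still be corrected before any accuracy result is reported.

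**What to change.** In section 2.7.3:

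1. Define sensitivity = a/(a+c).
2. Keep a/(a+b), but label it positive predictive value.
3. State that the positive and negative consistency rates equal sensitivity and specificity, or drop one pair of labels. After the correction the two pairs are identical.

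If predictive values are wanted as a pair, d/(c+d) can be added as the negative predictive value. This is optional.

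The cost is a line or so of text, with no new data and no change to conduct. There is time to do it: enrolment was extended to September 1, 2025, and three-year follow-up of patients enrolled near that date runs to about 2028 (2025 + 3).
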